### **8.2 SECONDARY EFFICACY VARIABLES**

To compare the effects of two routine treatments of AI, low dose prednisolone and standard regimens of hydrocortisone between Day 1 (pre-blinded treatment) and Day 120 (4 months post blinded treatment):

- Other markers of bone health
  - assessed by measurement of change in additional bone markers and bone profile including procollagen type-1 N-terminal propeptide (P1NP), bone specific alkaline phosphatase (BALP), corrected calcium, parathyroid hormone (PTH), vitamin D and urinary N-terminal telopeptide (NTX).

## PRED-AID Study Statistical Analysis Plan (SAP)

- Surrogate markers and risk factors for cardiovascular disease
  - including anthropometric markers such as: blood pressure, heart rate, BMI (height on first occasion), weight and waist-hip circumference ratio.
  - cardiovascular risk assessed by measurement of high-sensitivity CRP (hs-CRP), high-sensitivity troponin I, lipid profile and BNP.
- Glycaemic control
  - assessed by HbA1c, fructosamine, fasting glucose levels and insulin resistance represented by Homeostatic Model Assessment for Insulin Resistance (HOMA-IR)
- Infection rates and severity
  - assessed by completion of the German National Cohort Questionnaire (GNCQ)
- Immunology profiles
  - Assessed by measurement and assessment of soluble immunological analytes such as CD16 and isolated white cell populations including total white cells, neutrophils, lymphocytes, eosinophils, basophils, natural killer cells, and monocytes (including subtypes).
- Safety
  - assessed by reporting of symptoms of steroid deficiency and myopathy and review of routine monitoring blood tests including full blood count (FBC), renal profile, liver function tests (LFTs), creatine kinase (CK), Adrenocorticotrophic hormone (ACTH) cortisol binding globulin (CBG) and bicarbonate.
- Wellbeing
  - assessed by subjective health questionnaires including the SF-36 (7) and Addi-QoL (8)
- Compliance to regimen
  - assessed by collecting the remaining unused tablets at the end of each treatment arm

### 8.3 SAFETY VARIABLES

The safety variables measured in this study are included as part of the secondary efficacy variable and are reproduced below:

- Safety
  - assessed by reporting of symptoms of steroid deficiency and myopathy and review of routine monitoring blood tests including full blood count (FBC), renal profile, liver function tests (LFTs), creatine kinase (CK), Adrenocorticotrophic hormone (ACTH) cortisol binding globulin (CBG) and bicarbonate.

In addition, the number of adverse events (AE), serious adverse events (SAE), and SUSARs (suspected unexpected serious adverse reactions) will be recorded for each Study Period.

### 8.4 DEMOGRAPHIC VARIABLES

#### PRED-AID Study Statistical Analysis Plan (SAP)

The demographic variables to be considered in the analysis will at least include:

- Age
- Gender
- Weight
- BMI
- Cumulative daily dose of prednisolone required
- Cumulative daily dose of hydrocortisone required
- Type of AI (primary versus secondary)
- Number of anti-hypertensive agents (0, 1, 2,  $\geq 3$ )
- Use of a lipid agent
- Use of a bone sparing agent

## 9. STATISTICAL METHODOLOGY

### 9.1 GENERAL METHODOLOGY

Data will be collected and recorded throughout the study on both paper case record files and a validated database (Oracle InForm). Following last patient last visit and all data entry final data checks will be conducted. Post the resolution of any final data queries database lock will occur for analysis.

The main analysis will be conducted following the intention-to-treat principle and include all randomised patients, according to their randomised assignment for each period, irrespective of treatment actually received. A supplementary secondary per-protocol analysis will be performed for the primary outcome.

Since randomisation is stratified by type of AI (primary vs secondary) analyses of outcomes will involve adjustment for this factor, unless otherwise indicated. For continuous outcomes, baseline values of the outcome will also be adjusted for to increase power(9). For treatment period 1 the baseline outcome will be the outcome measured at the start of period 1. For period 2 the baseline should be from the assessments measure after the completion of period 1 and washout. This baseline definition will be applied to all analyses. Change from baseline will be calculated as post-baseline value – baseline value for the associated period.

Missing baseline covariate data are not anticipated since covariates must be recorded to allocate treatment. However, if there are missing values for baseline measure of a clinical outcome, they will be replaced by the mean of the observed baseline values for all participants in all treatment arms (mean imputation). This technique improves the statistical efficiency in the estimation of treatment effect and is justifiable since randomisation ensures that baselines are independent of treatment group(10).

Every effort will be made to obtain all follow up data for all participants, including those that have stopped treatment. All available data will be included within the analysis. The primary analysis model to be employed uses maximum likelihood estimation and is consequently efficient for handling missing outcome data under a MAR assumption. Where appropriate sensitivity analyses will be conducted to check that the conclusions are robust for, example, to the missing data assumption.

Although a washout period is incorporated into the design of the study to minimise carry-over effects, we will assess whether there is any evidence of a carry-over effect by fitting a separate linear mixed model which further includes the treatment by period interaction.

The continuous secondary outcomes will be analysed using the same modelling approach as specified for the primary outcome.

PRED-AID Study Statistical Analysis Plan (SAP)

All treatment effect estimates will be reported with 95% confidence intervals. A two-sided 5% level of significance will be used to assess the primary outcome. Statistical analysis will be conducted using SPSS or Stata.

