## 6.7 SAMPLE SIZE

The intention is to recruit 55 participants, allowing for a 20% drop-out rate. With 44 completers analysed there is a minimum of 90% power to detect a 1.5 µg/L effect on osteocalcin with a two-sided test at the 5% level of significance, assuming an estimate of the SD at a single timepoint of 3.0 (5). This assumes cautiously that the correlation between the repeated measurements within patients across the two periods is 0.5, whereas a previous crossover trial(6) showed a correlation of 0.8.

Following a pilot study to elucidate a reference range for osteocalcin in healthy volunteers and patients with AI, it has been shown that individuals can demonstrate reductions of up to 2.4 µg/L in the short

PRED-AID Study Statistical Analysis Plan (SAP)

term after changes in their steroid replacement regimen. It is anticipated that that larger changes in osteocalcin will be seen when patients continue on their new regimens for a longer duration.

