A carryover effect is not expected; therefore, the choice of a crossover design, the evaluation of efficacy by assessment of the change from trial baseline, and the proposed analysis model is considered to be appropriate. However, we will assess whether there is any evidence of a carry-over effect by fitting a separate linear mixed model which further includes the treatment by period interaction. In the case that there is a significant carry over effect we will fit a repeated measures linear mixed effect model using change from baseline in treatment period 1 (at 30 days and 120 days) as the dependent variable, a random participant effect, fixed effect for treatment, type of AI, baseline osteocalcin, use of bone sparing agent and time point. If this repeated measured model fails to converge, treatment effects for period 1 will be estimated using separate linear regression models for each follow-up time point, which include fixed effects for treatment, type of AI (primary vs secondary), baseline osteocalcin and use of a bone sparing agent.

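### The primary mixed model is specified as maximum likelihood with no small-sample degrees of freedom, so at 44 completers the 5% test and 95% CI are slightly anti-conservative

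*Combined protocol and SAP*

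**What the plan says.** SAP 9.1 names the estimator: "The primary analysis model to be employed uses maximum likelihood estimation". SAP 9.8 and protocol section 9 (methods of data collection and analysis) also name maximum likelihood, each time to justify handling missing outcomes under a missing-at-random (MAR) assumption. SAP 9.5 calls the model likelihood based without naming an estimator.

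Neither document mentions REML, Satterthwaite, Kenward-Roger, a t reference distribution or any other degrees-of-freedom rule. On software, SAP 9.1 says only: "Statistical analysis will be conducted using SPSS or Stata". The test is defined there too: "A two-sided 5% level of significance will be used to assess the primary outcome".

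SAP 9.5 specifies a repeated-measures model of change in osteocalcin at Days 30 and 120, with a random participant effect, unstructured residuals, and fixed effects for treatment, period, type of adrenal insufficiency (AI), baseline, bone sparing agent and time point. It adds a fallback: "In the case that there is a significant carry over effect we will fit a repeated measures linear mixed effect model", restricted to period 1. If that model does not converge, ordinary linear regression is used at each time point. SAP 9.6 applies similar mixed models to most secondary outcomes.

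**The concern.** ML divides residual variation by the number of participants rather than by that number less the parameters estimated, so the variance is biased downwards. If the test statistic is then compared with a normal distribution, the uncertainty in the variance is ignored as well. Both errors narrow the interval, and neither is negligible at 44 participants.

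The trial's main conclusion rests on the Day-120 treatment effect with its 95% CI and p-value. An analyst who follows the SAP literally would fit ML and would then have to choose a reference distribution that the plan does not give. The CIs of the secondary outcomes analysed with the same kind of model share the problem.

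**Working it through.** **Inputs from the documents.** SAP 6.7 gives "With 44 completers analysed", "The intention is to recruit 55 participants, allowing for a 20% drop-out rate", "assuming an estimate of the SD at a single timepoint of 3.0", a correlation of 0.5 between periods, and "minimum of 90% power to detect a 1.5 µg/L effect on osteocalcin with a two-sided test at the 5% level of significance". Allocation to the two orders is equal (protocol section 3).

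**The plan's own figure.**
- SD of the within-participant difference = 3.0 × √(2 × (1 − 0.5)) = 3.0.
- SE = 3.0/√44 = 0.452, so effect/SE = 1.5/0.452 = 3.32.
- Normal-approximation power = Φ(3.32 − 1.96) = 91.3%.
- Power with a noncentral t is 90.0% on 43 df and 89.97% on 42 df.
- Recruitment = 44/(1 − 0.20) = 55.

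The stated 90% is reproduced, even with a t reference.

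**Size of the test under ML.** For a contrast that uses k fixed effects on n participants, the ML Wald statistic is the usual t statistic multiplied by √(n/(n − k)). With critical value c, the true two-sided error is P(|t on n − k df| > c × √((n − k)/n)).

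- Crossover, n = 44, k = 2 (period and treatment, on within-participant differences): √(42/44) = 0.977. With z, the cut-off is 1.96 × 0.977 = 1.915, giving 6.2%. The correct critical value is 2.018, so the interval is 1.915/2.018 = 0.949 of its proper width. With the t critical value, the error is 5.5% and the width ratio 0.977.
- Counting the period-specific baseline as well (k = 3): 6.6% with z, 5.8% with t.
- Period 1 only, k = 5 (intercept, treatment, AI type, baseline, bone sparing agent): √(39/44) = 0.941. With z, the cut-off is 1.845 against 2.023, giving 7.3% and a width ratio of 0.912. With t, the error is 6.4%.

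**Simulation under the null.** This used the SAP 9.5 model with a treatment effect at each time point, a random participant effect, unstructured residuals within period, SD 3.0 and correlation 0.5 among all measurements. There were 5,000 trials at n = 44, with Monte Carlo SE about 0.3 points. The documents do not give the share with primary AI (40% assumed) or on bone sparing agents (20% assumed).

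| n = 44 | ML, z | ML, t | REML, t |
|---|---|---|---|
| Crossover, formula (k = 2) | 6.2% | 5.5% | 5% by construction |
| Crossover, simulated | 6.3% | 5.6% | 4.9% |
| Period 1, formula (k = 5) | 7.3% | 6.4% | 5% by construction |
| Period 1, simulated | 6.8% | 6.2% | 4.7% |

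The t columns use 42 df for the crossover and 39 df for period 1.

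**If more than 44 contribute.** SAP 9.5 takes all available follow-up, so n may approach 55. The formula then gives 6.0% (z) and 5.4% (t) for the crossover, and 6.8% and 6.1% for period 1. Simulation (2,500 trials, SE about 0.5 points) gives 6.7% and 6.0%, and 6.9% and 6.4%. The excess does not disappear at full recruitment.

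**The case against.** The strongest reply is that ML is mentioned only to support the MAR argument, and that the plan never commits to a z test. This is right as far as it goes. The part of the defect that the text fixes, ML itself, adds about half a point in the crossover analysis; the rest depends on a reference distribution that is not stated. A reader might infer that the plan as written carries 6% error, or 7% in the fallback. The documents do not support those as unconditional figures. What stands is that ML is the only estimator named and exceeds 5% with either reference.

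The fallback figures need further limits. They apply only after a significant carry-over test, and only to the first of the two period-1 models. If the unstructured residuals of the main model carry over, a random participant effect plus a 2 × 2 unstructured matrix on two observations per participant has four variance parameters for three identifiable quantities. Non-convergence, and hence ordinary regression, is then a realistic outcome, and that regression with its t test holds 5%. The figures also leave out any distortion from choosing the analysis by a carry-over test.

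Three other stronger readings are tempting:
- That the long list of covariates drives the error. The crossover contrast is within participants, and a between-participant factor such as AI type costs it essentially nothing.
- That a narrow interval would favour a claim of equivalence. The protocol's introduction speaks of equivalence, but neither document sets a margin, so no such claim is defined.
- That the p-value will differ between packages. The documents leave the options open, but nothing in them shows what either package would do.

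One uncertainty runs the other way. If the residual matrix is read as fully unstructured across all four follow-up measurements, ML with z simulates at 8.0%, and REML with t on 42 df at 6.4%. The text does not settle that reading, so 8.0% is not the headline. It does show why a degrees-of-freedom method should be named rather than a fixed number of df assumed.

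**Conclusion.** The point holds as a modest defect. With ML and 44 completers, the primary test has an error of about 5.5% with a t reference or about 6.2% with a z reference; with z, the 95% CI is about 5% too narrow. In the period-1 mixed model the error is about 6.2% to 6.4% with t and 6.8% to 7.3% with z, where the interval is about 9% too narrow by the formula.

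These figures assume residuals unstructured within period, a treatment effect estimated separately at Day 120 (SAP 9.5 reports one but does not list a treatment-by-time term), complete data on 44 participants, and the covariate frequencies assumed above. The excess is about half a point to just over two points of error, and the sample size is not affected. The change is worth making because the better method costs almost nothing and removes an analyst's choice from the main p-value.

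**What to change.** - In SAP 9.1, SAP 9.8 and protocol section 9, replace maximum likelihood with restricted maximum likelihood (REML). All three places must change, or the documents will contradict each other. SAP 9.5 does not contain the phrase.
- In SAP 9.5, applied also to 9.6, state that every mixed-model CI and p-value uses Kenward-Roger or Satterthwaite degrees of freedom. Choose one of the two, and cover the period-1 and carry-over models as well.
- In SAP 9.1, name one package in which the chosen method is available. Settle all of this before unblinding.
- State whether the unstructured residual matrix applies within period or across both periods.

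REML is also likelihood based, so the MAR justification stands. One practical consequence is that the carry-over term should be tested with its own F or t test, because REML likelihoods cannot be compared between models with different fixed effects.

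The cost is a few sentences and a software option. Relative to ML with z, the crossover interval becomes about 5% wider (1/0.949 = 1.054) and the period-1 interval just under 10% wider (1/0.912 = 1.096, the counterpart of being 9% too narrow). Relative to ML with t, the crossover interval widens by about 2% (1/0.977 = 1.024). No change to recruitment is needed.

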## **9.2 PATIENT FLOW (CONSORT DIAGRAM)**

PRED-AID Study Statistical Analysis Plan (SAP)

[figure not shown]

### 9.3 BASELINE DEMOGRAPHICS

Baseline characteristics will be reported according to treatment arm. Normally distributed continuous variables will be conveyed as mean (Standard Deviation (SD)), and median (Interquartile Range (IQR)) if non-normal. Categorical data will be reported using frequencies and proportions (as a %). The summaries will be based on observations only and the number of missing observations will be reported. No formal statistical tests will be performed since any differences between treatment arms at baseline will be the result of chance rather than bias, due to randomisation.

Concomitant medication will also be tabulated by treatment arm according to the general classification of the medication, as described in the British National Formulary (BNF). The number of participants in each arm using each medication will be reported.

#### **9.4 DESCRIPTIVE ANALYSIS**

Descriptive statistics will be presented for the primary and secondary outcome measures by treatment arm, period and time point.

#### **9.5 PRIMARY EFFICACY ANALYSIS**

As this is a two-period two-treatment crossover trial, the treatment effect will be estimated using a multi-level repeated measures linear mixed effect model. The change from baseline osteocalcin will be the dependent variable, at 30 days and 120 days. The model will include participant as a random effect and fixed effects for treatment and period, type of AI (primary vs secondary), baseline osteocalcin, use of a bone sparing agent, and time point (Day 30 and Day 120). An unstructured correlation matrix will be used for the residuals. The estimated treatment effect at 120 day will be reported with a 95% confidence interval and corresponding p value. The main conclusion of the trial will be based on this analysis time point. We will also report the treatment effect at 30 days.

The analysis will include all available follow-up data. The model is likelihood based and missing data will be assumed to be missing-at-random (MAR), conditional on the observed values of other variables included in the analysis. If there are missing values for baseline measure of a clinical outcome, they will be replaced by the mean of the observed baseline values for all participants in all treatment arms (mean imputation). Sensitivity analyses will assess the validity of the MAR assumption and address the impact of missing data for all patients if required (see Section 9.8).

Model assumptions, including the normality of residuals and random effects distributions will be assessed. If any assumptions are poorly met, then an appropriate transformation of the outcome (e.g. log transformation) will be considered.

If the repeated measured mixed effects model including both 30 and 120 day outcomes fails to converge, treatment effects will be estimated using separate mixed linear regression models for each follow-up time point, which include participant as a random effect and fixed effects for treatment and period, type of AI (primary vs secondary), baseline osteocalcin and use of a bone sparing agent. An unstructured correlation matrix will be used for the residuals.

A carryover effect is not expected; therefore, the choice of a crossover design, the evaluation of efficacy by assessment of the change from trial baseline, and the proposed analysis model is considered to be appropriate. However, we will assess whether there is any evidence of a carry-over effect by fitting a separate linear mixed model which further includes the treatment by period interaction. In the case that there is a significant carry over effect we will fit a repeated measures linear mixed effect model using change from baseline in treatment period 1 (at 30 days and 120 days) as the dependent variable, a random participant effect, fixed effect for treatment, type of AI, baseline osteocalcin, use of bone sparing agent and time point. If this repeated measured model fails to converge, treatment effects for period 1 will be estimated using separate linear regression models for each follow-up time point, which include fixed effects for treatment, type of AI (primary vs secondary), baseline osteocalcin and use of a bone sparing agent.

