#### Sample size

Fifty-five patients will be recruited, allowing for a 20% drop-out rate. With 44 completers analysed there is a minimum of 90% power to detect a 1.5 µg/L effect in osteocalcin with a two-sided test at the 5% level of significance, assuming an estimate of the SD at a single timepoint of SD of 3.0 (14). This assumes cautiously that the correlation between the repeated

measurements within patients across the two periods is 0.5, whereas a previous crossover trial(17) showed a correlation of 0.8.

Following a pilot study to elucidate a reference range for osteocalcin in healthy volunteers and patients with AI, it has been demonstrated that individuals can have reductions of up to 2.4 µg/L in the short term after changes in their steroid replacement regimen. It is anticipated that that larger changes in osteocalcin will be seen when patients continue on their new regimens for a longer duration.

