#### **9.6 SECONDARY EFFICACY ANALYSIS**

##### **9.6.1 OTHER MARKERS OF BONE HEALTH**

## PRED-AID Study Statistical Analysis Plan (SAP)

**Outcome definition:** Treatment arm difference in i) P1NP, ii) BALP, iii) Corrected calcium, iv) PTH, v) Vitamin D, vi) NTX from baseline to Day 120.

**Analysis:** A multilevel repeated measures linear mixed effect model will be used to estimate the treatment arm difference for each of the above bone markers from baseline to Day 120. Similar to the primary analysis model, the model will include fixed effects for time (2 categories: Day 30 and Day 120), treatment arm (2 categories: prednisolone and hydrocortisone), period, type of AI (primary or secondary), baseline outcome, use of a bone sparing agent. A random participant effect will be included and an unstructured covariance matrix will be used. The treatment effect at 120 days will be reported with a 95% confidence interval. The models assumptions about random effects distributions, correlation structure and residuals will all be investigated. If any assumptions are poorly met then log transformation of the analyte in question, will be explored. If the mixed effect model including both 30 and 120 day outcomes fails to converge, treatment effects will be estimated using separate mixed linear regression models for each follow-up time point.

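### SAP 9.5 omits treatment by time point, so the primary model gives one effect pooled over Day 30 and Day 120 instead of the Day 120 effect that decides the trial

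*Combined protocol and SAP*

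**What the plan says.** SAP 9.5 sets up one repeated-measures mixed model for both follow-up visits: "The change from baseline osteocalcin will be the dependent variable, at 30 days and 120 days". It has a random participant effect and "fixed effects for treatment and period, type of AI (primary vs secondary), baseline osteocalcin, use of a bone sparing agent, and time point". On the covariance it says: "An unstructured correlation matrix will be used for the residuals".

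The same paragraph then commits to two results specific to a time point. For the first, "The estimated treatment effect at 120 day will be reported with a 95% confidence interval and corresponding p value", and "The main conclusion of the trial will be based on this analysis time point". For the second, "We will also report the treatment effect at 30 days".

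If the joint model does not converge, 9.5 falls back on a separate model for each visit. If carry-over is significant, a period-1 model is fitted, again with treatment and time point as main effects. The secondary models in 9.6 follow the same pattern; in 9.6.1, for example, "the model will include fixed effects for time (2 categories: Day 30 and Day 120), treatment arm (2 categories: prednisolone and hydrocortisone), period", followed by further covariates. The lists in 9.6 are not identical to one another, but none contains treatment by time point.

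**The concern.** With treatment and time point entered only as main effects, the model assumes that the prednisolone minus hydrocortisone difference is the same on both days. One coefficient cannot supply two different effects, so the listed model and the promised results do not agree.

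The headline estimate, confidence interval and p-value are at stake: they would be labelled Day 120 while describing a mixture of the two days. What the trial estimates would also depend on the software. If the joint model converges, a pooled effect is reported; if it fails, the separate models give a true Day 120 effect. The sensitivity analysis (9.8), the per-protocol analysis (9.9.1) and the subgroup analyses (9.10) reuse the primary model and inherit the gap.

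**Working it through.** **1. Is the term supplied elsewhere?** The SAP names interactions where it wants them: treatment by period for carry-over (9.1 and 9.5) and subgroup by treatment (9.10). None involves time. Protocol section 9 lists treatment, period and type of AI. Its paragraph on secondary outcomes leaves the method for patterns over time to be chosen later. So the term appears nowhere.

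**2. The plan's own power figure.** Inputs from SAP 6.7: effect 1.5, SD 3.0, cross-period correlation 0.5, 44 completers, two-sided 5%, 20% drop-out.
- SD of the within-patient difference = 3.0 × √(2 × (1 − 0.5)) = 3.0.
- SE = 3.0/√44 = 0.452.
- Power = 90.0% (noncentral t, 43 df) or 91.3% (normal approximation).
- Recruitment = 44/(1 − 0.20) = 55.

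The stated figures reproduce, and they are for a comparison at a single time point.

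**3. What the listed model estimates.** Write τ30 and τ120 for the true effects on the two days. The generalised least squares estimate has expectation w·τ120 + (1 − w)·τ30, where

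w = (k² − rk)/(k² + 1 − 2rk).

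Here k is the ratio of the Day 30 to the Day 120 SD and r is the correlation between the two days. Both refer to the residuals after the participant effect or, equivalently, to the within-patient treatment differences. When k = 1, w = (1 − r)/(2 − 2r) = 0.5 for any r, which is the simple mean.

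**4. Illustration with equal variances.** The documents give neither a Day 30 SD nor a Day 30/Day 120 correlation. Assumptions: SD 3.0 on both days; correlation 0.5 between any two measurements in different periods; correlation ρ between the two days within a period, from 0.6 to 0.8. The variance of the averaged within-patient difference is (9 + 9 + 2 × 18 × (ρ − 0.5))/4.
- ρ = 0.6: 5.4, SE = √(5.4/44) = 0.350
- ρ = 0.7: 6.3, SE = 0.378
- ρ = 0.8: 7.2, SE = 0.405

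With a true Day 120 effect of 1.5 and 42 df (noncentral t):

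| True Day 30 effect | Reported as Day 120 | 95% CI covers 1.5 | Power |
|---|---|---|---|
| 1.5 (equal) | 1.50 | 95% | 95-99% |
| 0.75 (half) | 1.125 | 82-85% | 78-88% |
| 0.50 (one third) | 1.00 | 71-77% | 68-80% |
| 0 | 0.75 | 45-56% | 44-55% |

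The reverse case follows by symmetry. If the Day 30 effect is 1.5 and the true Day 120 effect is 0, the reported value is again 0.75 with the same SEs. The test then rejects 44-55% of the time instead of 5%.

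**5. Unequal variances.** The plan's unstructured matrix allows them. For k from 0.8 to 1.25 and residual correlation r from 0.6 to 0.8, w runs from 0.00 (k = 0.8, r = 0.8) to 1.00 (k = 1.25, r = 0.8). The half-effect case then reports 0.75 × (1 + w), from 0.75 to 1.50. On the scale of step 4, r = (ρ − 0.5)/(1 − 0.5) = 0.2 to 0.6. The range is then narrower: w = 0.16/0.68 = 0.24 to 0.8125/1.0625 = 0.76.

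**6. With the term added.** A calculation over the full list of fixed effects, plus treatment by time point, returns a Day 120 contrast of 1.50 with SE 0.453 whatever the Day 30 effect is. Power is 91.2% by the normal approximation, in line with step 2.

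**The case against.** The best defence is that this is a drafting omission. The paragraph promises a Day 120 effect, rests the conclusion on it, promises a Day 30 effect as well, and falls back on visit-specific models. An analyst who follows those sentences would have to add the interaction. The intention is probably as described, and that part stands. But the list of model terms is explicit, and coded as written it gives a pooled effect. Adding the term after unblinding would be an unplanned change to the primary model.

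Four stronger readings are tempting, and the documents do not support them.

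- *The plan contradicts its own expectation.* The sample size text anticipates that "larger changes in osteocalcin will be seen when patients continue on their new regimens for a longer duration". That compares with short-term reductions seen in individuals in a pilot study. It does not say that the difference between treatments grows from Day 30 to Day 120, and Protocol 1.2 expects equivalent outcomes.
- *The result is pulled toward no difference.* This is so only if the Day 30 effect is the smaller one. The reverse case in step 4 goes the other way.
- *The estimate is 25% too small.* That is the half-effect row with equal variances, which is one scenario among many.
- *The fallback models cannot be fitted.* A random participant effect plus an unstructured residual is over-parameterised only if the residual matrix spans the two periods, which 9.5 does not say. If it is the Day 30/Day 120 block within a period, it reduces at a single visit to one variance, and the model is identifiable.

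**Conclusion.** The point holds. As listed, the primary model cannot produce the Day 120 effect that decides the trial, or a separate Day 30 effect. This follows from the term list alone and needs no numerical assumption.

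The size of the error does depend on assumptions. There is no bias if the two effects are equal, and power then exceeds the plan. If they differ, the error is (1 − w) times the gap between them, in either direction. The table rests on equal variances, a cross-period correlation of 0.5 throughout, a within-period correlation of 0.6 to 0.8, and 44 participants with complete data. Its rows are scenarios and not predictions. The issue should be settled before unblinding because it concerns the primary estimate.

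**What to change.** Add treatment by time point to the joint model in SAP 9.5, to the period-1 model used after significant carry-over, and to every repeated-measures model in 9.6. State that the primary estimate is the prednisolone minus hydrocortisone contrast at Day 120 from that model, with its confidence interval and p-value, and that the Day 30 contrast is the additional result. Sections 9.8, 9.9.1 and 9.10 then pick up the corrected model by reference. Period by time point and baseline by time point are optional; treatment by time point alone delivers the contrast.

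The cost is SAP wording, model code and one extra parameter per model. The sample size stays as it is, because it already assumes a comparison at one time point.
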